**Methods:**

This is an ongoing, prospective, multicentre observational cohort study of patients with ILA referred from general health screening facilities with more than 70,000 annual attendances. Up to 500 participants will be enrolled annually over 3 years, with 5-year assessments every six months. Treatment intervention including anti-fibrotic agents will be introduced in disease progression cases. The primary outcome is the frequency of subsequent IPF or PPF diagnoses. Additionally, secondary and further endpoints are associated with the efficacy of early therapeutic interventions in cases involving disease progression, including quantitative assessment by artificial intelligence.

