## Methods/design

### Study design

This is a prospective, multicentre observational cohort study on ILAs diagnosed by respiratory specialists from general health screening facilities in Kumamoto Prefecture, Japan. Other details of the study’s design are as follows:

Presence or absence of invasion: Mild invasion (no new needle insertion with plasma blood sampling at enrolment:)Presence or absence of intervention: No intervention.Presence or absence of use of samples collected from the human body: Yes (plasma and serum are stored).Positioning of the study: observational study.Randomisation: None.

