Patients that show any signs of disease progression, including the appearance of clinical symptoms, decline in lung function, or exacerbation of HRCT findings evaluated by visual assessment and AIQCT [13], will be considered for a full work-up and the introduction of drug therapy. The detailed examination will include bronchoalveolar lavage (BAL), transbronchial lung cryobiopsy, or surgical lung biopsy. After registration, subsequent pulmonary complications requiring hospitalisation, such as acute exacerbation, pneumonia, pneumothorax, or lung cancer, will be recorded.

Furthermore, it will be recorded if long-term oxygen therapy is needed in cases of progression despite appropriate medication during the follow-up years. When therapeutic intervention is introduced, the assessment plan is reset, and regular assessments are carried out during the period from the introduction of treatment (Supplementary Table 2).

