#### Timing of the start of treatment

Regular mandatory check-ups are carried out every six months by a registered researcher at a medical screening centre and progression is assessed according to the Progressive Fibrosing-Interstitial Lung Disease progression criteria [15]. If deemed to be a progression, the facility MDD will also be consulted and a decision will be made to introduce therapeutic agents.

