### Statistical analysis

#### Sample size calculation

There are ≥ 70,000 examinees yearly for the Japanese Red Cross Kumamoto Hospital Health Care Center and the Center for Preventive Medicine of Saiseikai Kumamoto Hospital. The number of participants suspected of having ILAs was approximately 300 at each centre in 2018. Therefore, the total number of participants with ILAs is assumed to be approximately 600 per year.

According to the previous data, the number of cases will be underestimated by 10% because approximately 10% of the medical check-ups that require detailed tests for ILAs did not undergo the subsequent detailed examinations. Therefore, the maximum number of suspected ILAs is expected to be 500 cases annually.

Continuous variables will be expressed as means and standard deviation (SD), or medians and interquartile ranges (IQRs), and categorical variables for each group will be expressed as the number of subjects and percentages. The inter-observer variation in the presence or absence of HRCT findings will be analysed using the weighted kappa statistic and classified as follows: poor (κ = 0–0.20), fair (κ = 0.21–0.40), moderate (κ = 0.41–0.60), substantial (κ = 0.61–0.80), and almost perfect (κ = 0.81–1.00). Inter-observer variation regarding the extent of the HRCT findings was assessed using Spearman’s rank correlation coefficient. The HRCT scores assigned by the two independent observers are compared using the Bland–Altman method. If the HRCT patterns or scores do not agree between the two radiologists; one of the patterns or scores is adopted by consensus.

All analyses with ILA progression as the outcome variable are performed using logistic regression, where ILA progression was dichotomised with progression defined as probable or definite progression, and regression defined as no change, probable regression, and definite regression using subjective visual estimation as well as an objective AIQCT. Multivariable analyses will be adjusted for variables such as age, sex, and smoking status. In addition, a Cox proportional-hazards model has been created to assess treatment efficacy, considering the immortal period as a time-dependent covariate.

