## Discussion

This is the first prospective, multicentre, observational study to clarify (i) the aetiological data of patients with ILA from a large general health check-up population, (ii) the natural course of IPF or PPF from the asymptomatic stage, (iii) the effects and outcomes of early therapeutic intervention including anti-fibrotic agents for progressive cases of ILA, (iv) the new prognostic markers of ILA progression which are critical to better determine patients at a higher risk of IPF and PPF, and (v) the effectiveness of newer therapies for IPF on earlier ILA identification where therapeutic attenuation of functional decline will be more impactful than at the latter end stages of established IPF.

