### Specific MDD for cases progressing from the ILA stage and response to early therapeutic intervention

It has been reported that 20% of ILA cases progress within 2 years, and > 40% progress within 5 years [1, 2]. As well as increasing age, smoking history, BMI, and increasing copies of *MUC5B* promoter polymorphism being predictive background factors for ILA progression [3, 6, 11], the fibrotic signs of lung distortion, traction bronchiolectasis/bronchiectasis, and honeycombing on HRCT imaging are considered to be crucial for the progression of ILA and poor prognosis [10, 12, 17, 18]. However, there has been little data about how many patients are subsequently diagnosed with IPF or PPF. Furthermore, the natural history of the asymptomatic phases corresponding to the ILA stages in these progressive fibrosing phenotypes has not been elucidated. A recent meta-analysis showed that anti-fibrotic treatment reduces the risk of all-cause mortality in progressive fibrosing phenotypes, including IPF [8, 9]. However, it is critical to determine whether the early identification and diagnosis of these fibrotic ILDs could lead to early treatment, resulting in a better prognosis [5]. The present study’s flow is to assess the ILA stage every 6 months. Once clinical progression is confirmed, a full examination will be considered, including BAL and biopsy, according to the 2022 International Guidelines, and the degree of confidence in the MDD. Clarification on the progression from ILA to an advanced disease stage and treatment responsiveness in the respective pathologies of IPF and PPF is expected.

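### The Cox model for treatment efficacy names the wrong time-dependent covariate, and no control is named for progression, which triggers treatment

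*Protocol article*

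**What the plan says.** The protocol article gives one sentence on the efficacy model, in the statistical analysis section (under Sample size calculation): "a Cox proportional-hazards model has been created to assess treatment efficacy, considering the immortal period as a time-dependent covariate". It gives no outcome, time origin, risk set or comparator for that model.

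The sentence before it reads "Multivariable analyses will be adjusted for variables such as age, sex, and smoking status". It follows directly on the description of the logistic regression for ILA progression.

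Four places describe how participants come to be treated:

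- Abstract, Methods: "Treatment intervention including anti-fibrotic agents will be introduced in disease progression cases".
- Data collection: participants with signs of progression "will be considered for a full work-up and the introduction of drug therapy".
- Timing of the start of treatment: "If deemed to be a progression, the facility MDD will also be consulted and a decision will be made to introduce therapeutic agents".
- Study design: "Randomisation: None".

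The Abstract and the Discussion both list, among the study's aims, the effect of early treatment in ILA that progresses.

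**The concern.** There are two separate problems.

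First, the covariate is misnamed. In a time-dependent analysis the exposure switches from untreated to treated on the day treatment starts, and the waiting time before that day counts as untreated person-time. The immortal period is that waiting time. It is what the method has to allocate correctly, and is not itself a covariate.

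Second, coding treatment correctly removes immortal-time bias but not confounding by indication. Treatment is introduced after progression, so treated time is post-progression time. If untreated time is taken from the whole cohort, most of it comes before progression. The hazard ratio then mixes the effect of the drug with the effect of having progressed. A useful drug could look harmful, on a question that the article presents as one of its main aims.

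**Working it through.** The article gives no hazard ratio, event count or power for this model, so there is no figure of its own to reproduce. The check asks how large the bias could be if the model were fitted over the whole cohort with correctly coded time-dependent treatment and no progression term.

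**Input from the article.** The Discussion (section on MDD for progressing cases) states: "It has been reported that 20% of ILA cases progress within 2 years, and > 40% progress within 5 years". Taking 40% at 5 years, the progression hazard is −ln(1 − 0.40)/5 = 0.5108/5 = 0.102 per year. This implies a 2-year risk of 1 − exp(−2 × 0.102) = 18.5%, close to the quoted 20%.

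**Assumptions not in the article.** Event hazard before progression 0.01 per year; hazard multiplied by k = 1, 3, 5 or 10 after progression; true treatment hazard ratio 0.7 or 1.0; 50% or 100% of progressors treated, 0 to 6 months after progression; 5 years of follow-up.

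**Check by hand.** Ignoring deaths, the share of 5-year person-time before progression is (1 − 0.60)/0.5108 = 0.783. The other 0.217 is after progression.

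- If every progressor were treated at once, all untreated time would be pre-progression. The apparent ratio for a true 0.7 would be 0.7k: 2.1, 3.5 and 7.0 for k = 3, 5 and 10.
- If half were treated at once, untreated time would be 0.783 before and 0.1085 after progression, or 87.8% and 12.2%. The apparent ratio would be 0.7k/(0.878 + 0.122k): 2.1/1.24 = 1.7, 3.5/1.49 = 2.4 and 7.0/2.10 = 3.3.

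**Simulation.** 60,000 participants per scenario, with Cox models fitted in start-stop form. The delay to treatment puts some more post-progression time into the untreated group, so the values fall somewhat below those by hand.

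| k | True HR | Treated share | HR without progression term | HR with time-dependent progression |
|---|---|---|---|---|
| 1 | 0.7 | 50% / 100% | 0.66 / 0.74 | 0.66 / 0.69 |
| 3 | 0.7 | 50% / 100% | 1.51 / 1.98 | 0.66 / 0.73 |
| 5 | 0.7 | 50% / 100% | 2.18 / 3.09 | 0.71 / 0.63 |
| 10 | 0.7 | 50% / 100% | 3.20 / 5.51 | 0.75 / 0.69 |
| 1 | 1.0 | 50% / 100% | 0.93 / 0.92 | 1.04 / 0.87 |
| 3 | 1.0 | 50% / 100% | 2.33 / 2.78 | 1.07 / 0.85 |
| 5 | 1.0 | 50% / 100% | 2.95 / 4.58 | 1.00 / 1.06 |
| 10 | 1.0 | 50% / 100% | 4.35 / 8.25 | 1.00 / 1.03 |

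With k = 1 the model without progression is unbiased apart from simulation error. With k of 3 or more it reverses the direction of a beneficial effect. Adding time-dependent progression brings the estimate back to about the true value.

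**Limit of the check.** All simulated progressors have the same hazard, so sicker progressors are no likelier to be treated. The last column shows that accounting for progression removes this bias. It does not show that it removes confounding by severity among progressors, which needs its own adjustment.

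**The case against.** The strongest reply is that this is one sentence in a journal article. Outcome, risk set, time origin and covariates are commonly left to the full analysis plan, which is not shown. The sentence is most plausibly loose wording for the standard method of time-dependent treatment. The list of adjusters is open-ended and is attached to the logistic models, so it does not show that the Cox model omits severity. The aims speak of progressive cases, and treatment is a case-by-case decision after progression, so untreated progressors may exist and a progressor-only model is compatible with the text. All the event rates above are assumed. The treatment assessments listed under Further endpoints are before-and-after comparisons that do not need the Cox model.

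Most of this stands, and it rules out two stronger readings. A reader might infer that the model definitely compares treated progressors with untreated non-progressors and so cannot estimate a treatment effect. The article states no comparator, and the table shows that a Cox model with progression in it recovers the effect under the simulated conditions. A reader might also infer from the Discussion phrase "the effectiveness of newer therapies for IPF on earlier ILA identification where therapeutic attenuation of functional decline will be more impactful" that a comparison with established IPF is planned. That is rationale; no endpoint or analysis in the article sets up such a comparison.

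The reply does not dispose of the point. The covariate is stated, and stated wrongly. Reading the sentence charitably, as time-dependent treatment, still leaves progression uncontrolled in a study where progression triggers treatment.

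**Conclusion.** The point holds in a limited form. The time-dependent covariate is misnamed, and this follows from the text alone. The efficacy hazard ratio is also open to serious confounding by indication, because non-randomised treatment follows progression and no control for progression or severity is named for the model.

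The size is conditional. It requires a whole-cohort risk set, which the article neither states nor excludes, and a higher event rate after progression. With assumed 3- to 10-fold hazards, a true hazard ratio of 0.7 appears as about 1.5 to 5.5 and a null effect as about 2.3 to 8.3. If progression carries no extra risk, there is no bias.

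This should be fixed before the efficacy analysis is run. It does not touch the primary endpoint, the frequency of IPF or PPF diagnoses, or either listed secondary endpoint.

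**What to change.** State in the analysis plan:

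- Treatment status is the time-dependent covariate, 0 until treatment starts and 1 afterwards. Waiting time before the start counts as untreated.
- The efficacy comparison is limited to participants who meet the progression criteria, with time zero at the date first met. Alternatively, keep the whole cohort and include progression as a time-dependent term.
- The comparison is adjusted or weighted for severity at progression, using FVC, %DLco, HRCT extent and symptoms. The study already collects these.
- If few progressors remain untreated, outcomes after treatment are reported descriptively, without an efficacy claim.

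The cost is wording and analysis work. No new data and no change to clinical management are needed. A progressor-only comparison has fewer participants and a wider interval, and the efficacy claim may have to be dropped if the untreated group is too small.

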Furthermore, morbidity and mortality related to respiratory disease will be compared between groups using chi-squared or Fisher’s exact tests. Finally, variation in the global extent of ILA on HRCT examination between each evaluation timepoint will be compared between groups using the Mann–Whitney U or Wilcoxon tests. The extent of ILA according to a visual semi-quantified score or a quantified score by AI will be assessed by the Wilcoxon test for trends over time per case. The degree of progression for each diagnosed group of IPF or PPF will be compared with these scores using the Mann–Whitney U test.

Clinical laboratory evaluations will be expressed as mean, median, and interquartile range for each evaluation timepoint, and boxplots will be created for graphical representation. In addition, percentages of abnormal clinical laboratory results will be compared between the groups using chi-squared or Fisher’s exact tests. No interim data analysis has been planned.

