### Relationship between AI analysis for quantification of ILA on HRCT scans and clinical outcomes

AI and machine learning approaches have become increasingly important for quantifying and classifying ILA and fibrotic ILDs [13]. They will also help address the increasing demand for identifying the progression of ILA. In this study, quantitative assessments of ILA using AI will be combined with visual assessments that semi-quantify the visual extent of ILA in 5% increments, as well as the pattern of HRCT findings in line with the 2022 IPF international guidelines [7]. The presence or absence of progression will be assessed quantitatively using AI (AIQCT) and semi-quantitatively by visual assessment. The relationship between the degree of progression and HRCT pattern at enrolment and changes in lung function indices and serum markers will also be investigated.

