### Study limitations

First, since almost all patients suspected to have ILAs are asymptomatic, they may not necessarily visit a teaching hospital after referrals. For example, previous data from one of the check-up facilities (The Center for Preventive Medicine of Saiseikai Kumamoto Hospital) shows that the rate of missing re-evaluation was approximately 10%. Second, patients may fail to attend the regular 6-month visits after consenting to participate in the study because they are asymptomatic. Finally, a viral infection pandemic, such as COVID-19 or flu, might also affect regular visits every 6 months. For example, during the COVID-19 pandemic, patients feared the infection and tended to withhold regular hospital visits.

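### A Wilcoxon test is named for trends in serial ILA extent scores, but it compares two sets of values and gives no rate of change

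*Protocol article*

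**What the plan says.** The relevant text is in the Protocol article, Statistical analysis, printed under the Sample size calculation heading.

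- **Within patients:** both extent scores, visual and AI, "will be assessed by the Wilcoxon test for trends over time per case".
- **Between groups:** a rank test is used, either Mann–Whitney U or Wilcoxon: "variation in the global extent of ILA on HRCT examination between each evaluation timepoint will be compared between groups". The next comparison, between the IPF and PPF diagnosis groups, uses the Mann–Whitney U test. No other grouping is defined for the extent scores.
- **Models named:** logistic regression for progression reduced to yes or no, and a Cox model for treatment efficacy. No model is named for extent as a repeated measurement.
- **Schedule:** the Abstract describes follow-up "with 5-year assessments every six months". The six-monthly tests listed under Data collection do not include HRCT. The full schedule is in supplementary tables that are not shown, so the number of scans per patient is unknown here.
- **Data features:** Study limitations accepts that "patients may fail to attend the regular 6-month visits after consenting". The Discussion says that readers will "semi-quantify the visual extent of ILA in 5% increments".

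**The concern.** The purpose stated for the within-patient analysis is a trend. A signed-rank test asks whether paired differences between two occasions centre on zero; a rank-sum test asks whether two groups differ. Neither uses the order or spacing of three or more scans, and neither returns a rate per year. A patient with one of the two scans missing contributes nothing to a paired test, however many other scans exist.

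Two things are at stake. First, describing the natural course from the asymptomatic stage is a declared aim, and the named tests give p-values without a rate of change in extent. Second, the between-group tests are spread over timepoints with no key timepoint and no joint analysis. The reader must either treat each p-value at face value, or correct for their number, or rely on a single pair of scans. Each choice has a cost.

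**Working it through.** The Protocol article gives no alpha, effect size, SD or sample size for this analysis, so there is no figure of its own to reproduce. All inputs below, including two-sided 0.05, are assumptions, apart from the 5-year follow-up. Because the scan count is unknown, K = 2, 5 and 10 equally spaced follow-up scans after baseline are taken as the range.

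**1. False positives if every timepoint is tested uncorrected**

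With independent tests the chance of at least one p<0.05 is 1 − 0.95^K: 9.8%, 22.6% and 40.1% for K = 2, 5, 10. This is a benchmark only, because changes from a shared baseline are correlated. Two simulations with no true mean change (paired) or no group difference (two-group), using change from baseline at each scan, gave:

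| Setting | Test | K=2 | K=5 | K=10 |
|---|---|---|---|---|
| A | paired Wilcoxon | – | 19.7% | 28.5% |
| A | Mann–Whitney | – | 18.7% | 29.1% |
| B | paired Wilcoxon | 9.0% | 17.3% | 28.2% |
| B | Mann–Whitney | 9.2% | 17.9% | 28.9% |

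A: 2,000 runs, 100 patients (100 per group for groups), intercept SD 1, error SD 0.5. B: 1,000 runs, 100 patients (50 per group), intercept SD 4, slope SD 0.5 per year, error SD 2. In setting B a single slope analysis on all scans stayed near nominal: 5.3%, 5.2%, 5.6% for groups and 4.6%, 5.4%, 6.0% paired.

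**2. Precision if one pair of scans is used**

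Let s² be the between-patient slope variance and e² the error variance. The variance of one patient's estimated slope is:

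- first and last scan only: s² + 2e²/25
- all scans: s² + e²/Sxx, where Sxx = Σ(t − mean t)²

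Sxx is 12.5 for K=2, 17.5 for K=5 and 27.5 for K=10. With s = 0 the ratio is (2/25)·Sxx = 1.0, 1.4 and 2.2. These are the limits. With s = 0.5 the ratios shrink:

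| Error SD | First–last | All, K=5 | All, K=10 | Ratios |
|---|---|---|---|---|
| 0.5 | 0.25+0.020=0.270 | 0.25+0.014=0.264 | 0.25+0.009=0.259 | 1.02, 1.04 |
| 2 | 0.25+0.320=0.570 | 0.25+0.229=0.479 | 0.25+0.145=0.395 | 1.19, 1.44 |
| 4 | 0.25+1.280=1.530 | 0.25+0.914=1.164 | 0.25+0.582=0.832 | 1.31, 1.84 |

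With K=2 the least-squares slope is just (last − first)/5, so there is nothing to gain in precision.

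**3. Power**

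Setting B, two groups, slope difference 0.3 per year:

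| Analysis | K=2 | K=5 | K=10 |
|---|---|---|---|
| Rank test, last scan only | 49% | 47% | 48% |
| Rank tests, Bonferroni over timepoints | 42% | 34% | 33% |
| Slope on all scans | 52% | 58% | 65% |

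A noisier one-group example (60 patients, mean slope 0.3, slope SD 0.5, error SD 4) gave 46% for first-to-last against 58% for the slope with K=5, and 44% against 69% with K=10. A hand check for K=5 agrees: 0.3/√(1.530/60) = 1.88, so power is about Φ(1.88 − 1.96) = 47%; 0.3/√(1.164/60) = 2.15, so power is about Φ(0.19) = 58%.

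**The case against.** **The sentence can be read kindly.** A reader might infer that the trend is to be tested inside a single patient. On that reading one pair gives a smallest two-sided p of 2×0.5 = 1, and six non-zero differences are needed to get below 0.05 (2×0.5^6 = 0.031). The ordinary meaning, though, is paired by patient, which is a valid test for a chosen pair of scans. That stands, but no pair is chosen, and two scans are not a trend. Nor does taking the sentence to mean a Wilcoxon-type trend test on pooled ranks rescue it. That test assumes independent observations, and on simulated serial scans its size ran from about 0% to 16%.

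**HRCT progression already has an analysis.** Logistic regression covers it, and a progression rate can mean a proportion of cases. This is right as far as it goes. It answers how many progressed, not how fast extent changed, and the trend sentence concerns the scores themselves.

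**Time since enrolment may be misaligned.** The Data collection section says "When therapeutic intervention is introduced, the assessment plan is reset", and a reader might infer that treated and untreated patients are compared at visits that fall at different times. The documents do not support stating this. The groups are not defined as treated versus untreated, timepoints are not defined by visit number, and the post-treatment schedule is in a table that is not shown.

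**The size depends on chosen inputs.** This stands. The power loss almost disappears with error SD 0.5 or with two follow-up scans, and the false-positive figures assume that any single p<0.05 would be taken as a finding, which the article does not say.

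**An unseen analysis plan may name a longitudinal model.** It may, but the article itself assigns this test to this purpose.

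**Conclusion.** The point holds in a limited form. The article names, for trends in serial visual and AIQCT extent scores, a test that can neither test nor estimate a trend over more than two scans, and no other stated analysis gives a rate of change in extent. That conclusion needs no assumption about inputs.

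The numerical cost is conditional. Uncorrected testing at every timepoint carries a chance of at least one false p<0.05 of about 9%, 17–20% or 28–29% with 2, 5 or 10 follow-up scans. Using one pair of scans costs between almost nothing (small measurement error or few scans) and a material amount of power (large error, many scans). A reader might infer that the plan suffers inflation and power loss together; it does not, since the first arises without correction and the second with correction or a single pair.

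Only further endpoints are affected. The primary endpoint, the frequency of IPF or PPF diagnoses, and the secondary frequencies are untouched. The change should be made, but the study does not stand or fall by it.

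**What to change.** For each extent score (visual and AIQCT), make the main trend analysis a mixed model that uses all scans at their actual dates, with random intercept and slope per patient and a group-by-time term. Report slopes and slope differences with 95% CIs. If the visual score, recorded in 5% steps, fits poorly, use a transformed or ordinal version. Keep the rank tests for one prespecified pair of scans or as descriptive checks.

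Report any change in slope at treatment start as descriptive only. The section on the timing of treatment ties its start to judged progression, so a before–after change in slope is open to regression to the mean.

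The cost is revised analysis wording, a little more programming and a model assumption to check. Patients with some missed scans still contribute, and no new data are needed.
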